**Discussion:**

If either the Local Opinion Leader Statement or the Unsigned Evidence Statement improves secondary prevention in patients with coronary disease, they can be easily modified and applied in other communities and for other target conditions.

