#### Primary outcome

The primary outcome measure is a composite measure representing improvement in statin-related secondary prevention consisting of: 1) provision of a statin sample, or 2) provision of a statin prescription, or 3) increasing the dosage of a statin within the first six months post-angiogram. As this is a composite end-point, only the first event attained in the cluster will be counted for analysis, although all events will be recorded in the database.

Six months was chosen for the primary and secondary outcomes because the average number of physician visits in our audit of trial-eligible patients attending the University of Alberta cardiac catheterization laboratory in the 2003 year was 1.8 visits in six months. As we are assessing the impact of the Local Opinion Leader Statement and Unsigned Evidence Statement on physician practice patterns, for the purposes of this study we are interested solely in evaluating attempted practice change. In other words, if a patient is provided with a statin sample or a statin prescription, or the dosage is increased by any of the patient's physicians, it would still count as a positive outcome for the main study analysis, even if the patient cannot tolerate the medication and discontinues it or is noncompliant during follow-up. We recognize that patient (and physician) long-term compliance with preventive therapies is important, and will collect data on persistence rates with secondary prevention maneuvers over the six months of the study. We anticipate that this data will serve as pilot data for a planned future study on interventions to improve provider/patient persistence rates.

We will examine the primary outcome rates in all three treatment arms as follows: the primary comparison will be between those patients randomized to the Local Opinion Leader Statement versus usual care, and the secondary comparisons will be (a) between those patients randomized to the Unsigned Evidence Statement versus usual care, and (b) between those patients randomized to the Local Opinion Leader Statements versus Unsigned Evidence Statements.

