### Sample size

In a survey of 22 members of the divisions of cardiology and general internal medicine at the University of Alberta, we determined that the "minimal" clinically important difference for this particular intervention to be considered useful was a 15% absolute improvement over and above usual care. After six months, we estimate that no more than 20% of control patients will have attained our composite primary outcome, given that patients who are already on a statin and have optimal LDL cholesterol levels will be excluded from this study at baseline. We calculated our sample size to detect a 15% absolute increase in the primary outcome, set the α error rate at 0.05 (2-sided), and the β error at 0.20 (power 80%) – this yielded a sample size of 138 patients per study arm. Allowing for losses during follow-up, the ability to examine each of the conditions separately, and the possibility of a very small design effect associated with patient clustering, the total sample size has been adjusted upwards to 160 patients per arm (480 in total).

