### Statistical analyses

Intention-to-treat analyses will be carried out with patients as the unit of analysis. Although the physician will be the unit of allocation, we anticipate a very small design effect, and the outcomes for individual patients will be clinically and statistically independent of each other.

The primary outcome will first be tested using the chi square statistic to compare the attainment of our primary statin outcome within six months in patients randomized to the Local Opinion Leader Statement versus patients randomized to the Unsigned Evidence Statement. If the impact of the Local Opinion Leader Statement is significantly different from that of the Unsigned Evidence Statement, we will compare each to usual care separately. If the impact of the Local Opinion Leader Statement and the Unsigned Evidence Statement are similar, we will combine data from both arms and compare this with usual care, which will essentially be a test of point-of-care reminders versus usual care.

In order to investigate what factors are associated with changes in the primary outcome (our dependent binary variable), and to control for the possibility of potential imbalances in patient-level characteristics at baseline, multivariable logistic regression analyses will be used to examine those variables that are deemed to be clinically important (i.e., age, gender) or that differ statistically at a p-value < 0.10 between study arms. In addition, to examine the possibility of "cluster-associated" study design effects, two sensitivity analyses will be considered. First, the main analysis will be repeated using the physician as the unit of analysis. Second, the aforementioned logistic regression models will be reanalyzed using generalized estimating equations to control for the potential lack of statistical independence among patients treated by the same study physician[84].

There will be one pre-planned interim analysis to explore event rates in all three study arms after 80 patients per arm have reached the six month primary outcome time-point. We are primarily interested in examining whether projected event rates are correct, or whether the sample size will need to be adjusted upwards, and will employ the Haybittle-Peto stopping rule using a Z value of 3.0 for this interim test. For the main study analysis, we will consider a p-value < 0.05 to be statistically significant.

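### The ranking of the three comparisons does not govern the testing: the written sequence runs each test at p<0.05 without gatekeeping, so the chance of any false rejection is about 9.7%, and 6.6% against usual care

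*Protocol article*

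**What the plan says.** Three parts of the protocol article bear on this.

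- **Ranking.** Aim of the study states one principal hypothesis, signed statement versus usual care, and two secondary ones. Primary outcome repeats this. It names signed versus usual care as the primary comparison and adds that "the secondary comparisons will be (a) between those patients randomized to the Unsigned Evidence Statement versus usual care" and, as (b), signed versus unsigned.
- **Testing.** Statistical analyses starts with a chi-square test of signed versus unsigned. If they differ significantly, each is compared with usual care. If they are similar, the two arms are pooled and compared with usual care. The final threshold is given once: "For the main study analysis, we will consider a p-value < 0.05 to be statistically significant".
- **Sample size.** "We calculated our sample size to detect a 15% absolute increase in the primary outcome", with the investigators having "set the α error rate at 0.05 (2-sided"). That is a single two-arm contrast: "this yielded a sample size of 138 patients per study arm", raised to 160 for losses and other allowances.

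Nothing makes the secondary comparisons depend on the primary one, divides alpha, or limits what may be claimed when the primary comparison fails or is not run.

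**The concern.** A ranking of comparisons protects the error rate only if it decides which tests may be claimed as confirmatory. Here it does not. The comparison ranked first is not tested first, and it is tested separately only when the two statement arms differ significantly. A test against usual care is reached on both branches, so the opening test does not act as a gate.

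The 5% in the sample size section therefore describes one contrast taken alone. It does not describe the procedure the plan will carry out. A nominally significant result could be reported at the 5% level from a procedure with a larger false-positive rate, and the plan does not say what standing such a result would have.

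**Working it through.** **Inputs**
- Two-sided alpha 0.05, power 80%, 20% versus 35%, 138 per arm raised to 160 (Sample size).
- 1:1:1 allocation (Allocation to experimental arms).
- Test order and threshold (Statistical analyses).
- Assumptions: the global null at a 20% event rate, the article's ceiling for usual care; similar read as not significant at 0.05; patients independent; no losses; the single interim look at Z = 3.0 ignored because it adds very little.

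**1. The plan's own figure.** Pooled-variance formula, mean proportion 0.275:

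n = [1.960·√(2·0.275·0.725) + 0.842·√(0.20·0.80 + 0.35·0.65)]² / 0.15² = (1.2377 + 0.5239)² / 0.0225 = 137.9, so 138.

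This matches exactly. Power at 160 per arm is 85.5%. The calculation covers one contrast and makes no allowance for others.

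**2. Any false rejection under the written sequence.** Let L, U and C be the observed proportions in the signed, unsigned and usual-care arms, with equal variance v under the null. The first contrast is L − U and the pooled contrast is (L + U)/2 − C. Their covariance is v/2 − v/2 = 0, so the two tests are independent in large samples. A false rejection occurs if the first test rejects, or if it does not and the pooled test does:

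1 − 0.95² = 9.75%.

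Binomial simulation (2 million trials, 160 per arm, 20%, uncorrected chi-square) gives 9.7%; 4 million normal draws give 9.8%.

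**3. False rejection against usual care.** This is the error that would credit a statement with an effect. From the same simulations:
- first test significant and at least one arm differs from usual care: about 1.9%
- first test not significant and pooled arms differ from usual care: about 4.7%
- total: 6.6% two-sided
- in the beneficial direction only: 3.1%, where a single two-sided 0.05 test would give 2.5%

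**4. Comparators**

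| Procedure, global null | Error rate |
|---|---|
| Primary comparison alone | 5.0% |
| Written sequence, any rejection | 9.7% |
| Written sequence, rejection against usual care | 6.6% |
| Both statements versus usual care, run together unadjusted | about 9.0% |
| All three pairwise tests, run together unadjusted | 12.1% |
| Fixed sequence led by the primary comparison | 5.0% |

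The 9.0% and 12.1% rows would apply only if the comparisons under Primary outcome were all run side by side. Statistical analyses does not do that.

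**5. Sensitivity to the event rate.** From 10% to 40%, the any-rejection rate of the written sequence stays between 9.6% and 9.8%, and the rate against usual care at 6.6% to 6.7%.

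**6. How often the primary comparison is run.** If the two statements are equally effective, the first test is significant about 5% of the time, so signed versus usual care is tested separately in only about 5% of such trials.

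**The case against.** The strongest reply is that the article designates one primary comparison and sizes the trial on it. For that comparison alone 5% is correct, and leaving secondary comparisons unadjusted is common practice. It can be added that multiplicity detail often sits in a statistical analysis plan, which is not shown here. The first part stands as far as it goes: a reader might infer that the plan has no hierarchy, and that would be wrong. The second part does not answer the point, because the article itself fixes the tests, their order and the threshold, and that combination does not hold 5%. The designation also gives little comfort when the designated comparison is run separately only after a significant signed-versus-unsigned test.

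Two stronger readings should be set aside.

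- A reader might take 9% to 12% as the chance of wrongly concluding that either statement works. Those figures assume simultaneous pairwise tests. Under the written sequence the error against usual care is 6.6%, and about 3.1% in the direction that would support using a statement. The 9.7% also counts false signed-versus-unsigned differences. Counting them is reasonable, since that contrast is a stated secondary hypothesis, but such a difference does not show that a statement beats usual care.
- A reader might treat the abstract's discussion, "If either the Local Opinion Leader Statement or the Unsigned Evidence Statement improves secondary prevention", as a decision rule giving two chances of success. The sentence goes on to say that the statements could then be applied in other communities and conditions. It is a remark on generalisability and sets no criterion for success.

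Nor can unsigned versus usual care come out significant on its own after a failed signed comparison, unless signed versus unsigned was significant first.

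**Conclusion.** The point holds in limited form. The comparisons are ranked, but the ranking has no effect on the tests, and the sequence in Statistical analyses does not control the error rate at the stated 5%. Its size is about 9.7% for any false rejection and about 6.6% two-sided (3.1% beneficial) for a false rejection against usual care.

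The figures rest on the global null, 160 analysed patients per arm and independent patients; clustering is ignored. The any-rejection figure depends very little on the assumed event rate, because it follows from the independence of the two contrasts. The excess in the direction that matters for adoption is modest. The case for change rests as much on making sure the declared primary comparison is run as on the inflation.

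**What to change.** In Statistical analyses, replace the branching rule with a fixed sequence on the statin composite. Each step is at two-sided 0.05 and is tested only if the previous step is significant:

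1. signed statement versus usual care
2. unsigned statement versus usual care
3. signed versus unsigned statement

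After the first non-significant step, report the remaining contrasts as estimates with 95% confidence intervals, labelled exploratory. Report the pooled-arms contrast in the same way throughout.

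**Cost.** One paragraph of text. The primary comparison keeps full alpha, so 138 (raised to 160) per arm is unchanged. By contrast, a Bonferroni split would need 168 per arm for the two usual-care contrasts (power at 160 would be 78.1%) or 185 for all three.

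There are two real losses. The secondary contrasts cannot be confirmatory if the signed statement fails against usual care. The pooled test is also no longer confirmatory. When both statements reach 35% against 20% in usual care, it compares 320 with 160 patients and has power of about 94%, against about 86% for signed versus usual care alone.

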#### Other analyses

In examining the secondary outcomes (for example, use of ACE inhibitors, beta-blockers, etc.), we will use similar statistical methods for the primary statin outcome analyses.

### Data management

All data will be collected using standardized data sheets and data collation, entry and quality assurance will be carried out in the Epidemiology Coordinating and Research (EPICORE) Centre, Division of Cardiology, University of Alberta.

### Ethical considerations

Each patient will be given written information about the study and written informed consent will be obtained prior to study entry. Although the physicians receiving our study faxes will not be explicitly informed that they are in a trial at the time of the fax, we did inform all physicians with privileges within participating health authorities at the time of the opinion leader survey that a trial testing novel strategies to communicate evidence for patients with coronary artery disease would be conducted in the near future. On the survey form eliciting the opinion leaders, we gave all physicians the option to indicate if they did not want to participate in this future region-wide program to improve prescribing practices for CAD. Those who declared they did not want to participate were excluded from ESP-CAD eligibility. Thus, any patients of these physicians will not be enrolled in ESP-CAD. Furthermore, it should be noted that as part of the process of obtaining privileges within the participating health authorities (the Capital Health Authority in Edmonton and the Calgary Health Region) physicians sign a consent form to participate in "peer review and clinical quality improvement programs" within the health authorities, and such forms are updated every three years.

The study protocol has been approved by the Health Research Ethics Board, University of Alberta, Edmonton, Alberta (file number: 5082) and the Conjoint Health Research Ethics Board, University of Calgary, Calgary, Alberta (ethics ID: E-20129). The funding for the study is from three peer-reviewed grants. The funding sources (the Alberta Heritage Foundation for Medical Research, the Heart and Stroke Foundation of Canada, and Pfizer Canada) had no role in the design of the study and will have no role in its conduct, analysis, interpretation, or reporting – and will not have access to the data. None of the local opinion leaders received any financial compensation for their participation in the study or endorsement of the evidence summaries.

## Discussion

We report the protocol of a cluster randomized trial that aims to determine the effect of a feasible and readily generalizable evidence-based quality improvement initiative for patients with CAD. Local opinion leaders are potentially powerful tools for quality improvement, and our proposed method of defining a role for them in cardiovascular disease should lead to improved care for patients. In addition, this trial will establish whether the APPROACH computer system can be used as a novel vehicle for identifying and delivering secondary prevention interventions to high-risk patients with CAD. If our interventions are effective, they can be widely and easily applied in other communities, particularly in the future as APPROACH extends beyond the borders of Alberta, as well as for other target conditions.
